#### Monthly assessments

Details of the Monthly Assessments (e.g., questionnaire titles, details, psychometric information, references) are in the Additional file 1: Psychometrics and References for Self-Report Measures. The maximum number of Monthly Assessment questions is 293, determined by participant responses to header questions. Average completion time for each Monthly Survey is 32 min. All Monthly Surveys also assess for: (1) symptoms of PTSI including generalized anxiety disorder, major depressive disorder, panic disorder, PTSD, and social anxiety disorder, as well as PTSI correlates (e.g., substance use, chronic pain, insomnia); (2) individual differences associated with PTSI: (a) PPTE exposures; (c) resilience; (d) mental health care knowledge, access, and use; (e) occupational stressors, social support, and self-care; and (3) ERST retention and use. Participants receive written (through the Portal) summaries of their Monthly Assessment including timeline charts for participants to monitor fluctuations, facilitating participation healthy habits [90–92]. Responses consistent with one or more mental disorders are flagged for participants and include recommendations for accessing additional mental health supports.

#### Daily assessments

The Daily Assessments are very brief self-report questionnaires that allow participants to reflect and report on the past 24 h for (1) Mood, Attitude, and Performance; (2) Physical Wellness; (3) Emotional State; (4) Work Hours; (5) Sleep Hours; (6) Sleep Quality; (7) Eating; (8) Physical Activity; (9) Social Activity; (10) Substance Use and Gambling; and (11) ERST use. Mood, Attitude and Performance, and Physical Wellness are rated on 100-point visual analogue scales with anchors of ill (0–25), injured (26–50), reacting (51–75), and healthy (76–100). A 24-point rating scale is used for Emotional State, Work Hours, and Sleep Hours. Sleep Quality, Eating, Physical Activity, Social Activity, and Substance Use is reported dichotomously (i.e., yes/no), with discretionary options for participants to record details. The Daily Assessments also allow participants to log PPTE or other significant emotional events, creating a record of exposures to stressors. Average completion time for each Daily Survey is ~ 1 min. Completing the Daily Assessments supports regular self-reflection and provides participants with graphical feedback to facilitate healthy habits [90–92].

#### Biometric assessments

The LLA Recordis™ cardiac sensor device (LLA Technologies Inc., Langley, BC, Canada) is used to collect timing data that are similar in quality to M-mode echocardiography timing events (i.e., systole, diastole, isovolumic contraction and relaxation periods, rapid ejection), as well as twist forces of the ventricle (i.e., surrogate for contractility), heart rate variability (i.e., low frequency, high frequency, low frequency/high frequency ratio, square root of the mean of the squares of the successive differences between adjacent NNs), and Myocardial Performance Index variant [93]. The Recordis™ is applied to the sternum base (~ 1 cm above the xiphoid process) with a single electrocardiography electrode or heart belt strap, and uses a smartphone application providing immediate and ongoing user feedback. The current protocol requires a 1-min recording upon waking, with data downloaded for off-line processing and analyses. Briefly, previous research using echocardiography, the “gold standard” for cardiac function analysis, has demonstrated that individuals with PTSD have reduced diastolic function [94]. The LLA Recordis device can be used to record cardiac timing [95] events synonymous with echocardiography (e.g., diastole, systole, isovolumic relaxation, and contraction time).

### Data management and confidentiality

Data transfers from participant devices to secured research servers in Canada are protected using Transport Layer Security. The PSP PTSI Study also employs a PKI Class 3 SSL Certificate, with a 2048-bit digital signature and 256-bit encryption. Data stored on the servers are automatically encrypted using server-side Advanced Encryption Standard–256 encryption before being saved to disk and decrypted before data are downloaded. The data are stored separately from the data dictionary and the codes necessary for interpretation.

Study participants are guaranteed confidentially, but not anonymity. Participants provide an email address to manage their interaction and communication with the study. Participant email addresses are then used to log into the study portal and to connect participants with the surveys presented through the study portal. Individual survey results are not available to anyone outside the individual participants who can view their own data and the study team. During the study, the data are accessible only to the study team. Study data are not available to PSP employers.

Participant confidentiality is reviewed at the beginning of each clinical interview, including limitations: (1) imminent risk of harm to self or others; (2) disclosures of child abuse; and, (3) court subpoenas. Participant disclosures of suicidal behaviours during the clinical interview were followed by a SAFE-T Suicide Risk Assessment [96]. Each PSP sector also provided a contact person to call if a participant was at imminent risk of suicide and where necessary 9–11 will be contacted. All participants who reported suicidal thoughts or behaviours were invited to create a safety plan including identifying a specific support plan (e.g., friends, family, significant other, mental health crisis line, 9–11), healthcare professionals and services, and decision planning for when to reach out for help. Participants were also reminded about factors for suicide risk (e.g., alcohol, substance use) and resilience (e.g., social supports, reasons to live).

### Hypotheses

The PSP PTSI Study was registered with ClinicalTrials.gov (i.e., identification code NCT05530642), and the hypotheses were pre-registered.^1^ Hypotheses specific to individual difference variables are provided in Additional file 1: Tables (i.e., PTSI Measures; Primary Individual Differences Associated with Posttraumatic Stress Injuries; Secondary Individual Differences Associated with Posttraumatic Stress Injuries). Overarching PSP PTSI Study hypotheses:Participant mental health disorder prevalence rates at T1, based on Clinical Interviews or screening tools based on self-reported symptoms, will be higher than the general population [3, 97].From T1 to T2, participants will evidence reductions in risk, increases in resiliency, and improvements in mental health, as a function of the ERST [98, 99].Participants will evidence statistically significant predictive relationships between completing assessments and changes to individual differences over time (i.e., inversely with risk, positively with resilience, positively with mental health).Participants will evidence statistically significant sequential predictive relationships for environmental factors or individual differences reported during the *Daily Assessments*, *Monthly Assessments*, and *Full Assessments*.All participants will evidence sustained reductions in risk, increases in resilience, and increases in mental health at T3 relative to T2.Participants will evidence a statistically significant relationship between changes in individual differences over time and engagement with ERST content.Participants will evidence a statistically significant relationship between changes in environmental factors or individual differences over time, frequency of exercise [100], and other self-reported indicators of physical health [101].Relative to men, women will report more difficulties with mental disorder symptoms and occupational stressors.Diastole will be reduced in PSP who report symptoms consistent with one or more PTSI.The biometric data will be statistically significantly and substantively correlated with measures of PTSI.There will be a statistically significant and substantive relationship between PTSI symptom severity and reduced diastolic function.Changes in biological variables (i.e., autonomic nervous system reactivity, heart rate variability, cardiac mechanical changes) will be associated with environmental factors or individual differences.

### Planned analyses

Study data will initially be described using frequencies, means, and standard deviations. Missing data will be described within and across measurement occasions. Multiple imputation will be adopted assuming a missing at random mechanism [102]. Strategies will be adopted to control the familywise error rate (i.e., the probability of at least one Type 1 error in a family of tests) [103], while accounting for Type 2 errors [104]. Analyses will include mixed-effects multiple linear and non-linear regression models including covariates (i.e., sex, age, marital status, education, province of residence) and trend analyses as needed. To test for differences between PSP sectors in the cross-sectional analyses, a mixed-effects model will be used that accounts for clustering within PSP sectors. To test for changes over time, a mixed-effects model will be used that accounts for clustering within PSP sectors as well as within individuals (i.e., repeated measurements for each individual). Recursive Bayes algorithm and ecological momentary analyses will be used to analyze the Daily Assessments and biometric data. Quantitative analyses will be disaggregated for both sex and gender. Qualitative data (survey and focus group) will be coded using conventional qualitative content approaches [105] for inductive identification of themes.

### Knowledge translation

Main results will be shared with the research community via publication in peer-reviewed journals. Results will be of interest to PSP stakeholders (e.g., members, families, leadership), clinicians, policy planners, and governments; as such, knowledge translation efforts will be tailored for different audiences. Technical reports and lay summaries will be available through the study website (www.saskptsistudy.ca), and provided to the PSP knowledge users, the PSP focus groups, and the PSP partner agencies involved in the PSP PTSI Study, as well as provided to the Department of Public Safety and Emergency Preparedness. Results will be communicated to PSP stakeholders through the Canadian Institute for Public Safety Research and Treatment (www.cipsrt-icrtsp.ca) knowledge translation channels, and the University of Regina Communications Department will issue press releases as appropriate.

### Current study status and impacts of COVID-19

Recruitment began after a study launch meeting with the PSP sector leaders on September 22, 2020. COVID-19 substantially impacted the timelines for recruitment and training, as well as increasing the workload for all PSP, which reduced the individual capacity of participants to engage with novel training. In March 2021, a Steering Committee consisting of the PSP sector leads and the research team leads was established and recruitment began in earnest. Steering Committee meetings were held monthly for continued assistance with recruitment. Data collection began on October 20, 2021. T1 data collections for all participants were completed May 23, 2022. The T2 data collections for all participants are expected to conclude by August 19, 2022. The T3 data collections for all participants are expected to conclude by September 16, 2023.

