### Gender and sex

Gender and sex-related factors may affect PSP work experiences and mental health. In a recent large pan-Canadian, pan-PSP study, women in policing and firefighting reported higher prevalence rates of posttraumatic stress disorder (PTSD) and other mental health disorders; however, the differences were not statistically significant for correctional workers or paramedics [3]. Women continue to be under-represented across most PSP sectors in Canada [74]. Existing research has documented concerns about hyper-masculinity and sexual harassment affecting women in policing [75–78], and recent high-profile legal cases have highlighted ongoing sexual harassment and assault in Canadian policing [79] and corrections [80], and amongst American paramedics [81]. Gendered ideologies linking physical strength with competency may further sideline female officers [82]. Women PSP experience such work-related stressors in combination with other gendered stressors in everyday life. For example, women in Canada continue to perform disproportionate amounts of domestic and caregiving work [83], which creates specific challenges for women accessing parental leave and balancing work with caring responsibilities [25, 84].

The researchers will convene eight subsequent sector-specific focus groups after T2 (i.e., immediately after program completion), separated by position (i.e., frontline, leader) and sector, to support evaluating the training content, delivery, and impact. The eight focus groups will also identify any differential experiences of the training based on PSP sector or other variables, including gender, identify causal factors, and propose solutions for future training where appropriate. The eight focus groups will include both men and women; however, two additional separate focus groups will be convened, one for women across all PSP sectors and one for men across all PSP sectors, to identify gender dimensions of PSP experiences. The result will be a total of 11 focus groups for the current study (i.e., *n* = 1 initial; *n* = 8 after T2; *n* = 2 after T2).

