### Data collection time frame

Participants will each be assessed for a period of at least 16 months to identify pre-training, post-training, and follow-up results associated with ERST. Study assessments occur in four main categories (see Tools and Measures for details): Full Assessments, Monthly Assessments, Daily Assessments, and Biometric Assessments. The data collection time-period broadly uses three milestones: pre-training (i.e., T1), post-training (i.e., T2; ~ 16 weeks after training commences), and a follow-up 1 year after T2 (i.e., T3). Each milestone involves a Full Assessment (i.e., FA1 to FA3). Data collection concludes at FA3. Participants complete their first Monthly Assessment (i.e., MA1) approximately 4 weeks after completing FA1 and do not complete a Monthly Assessment concordant with a Full Assessment (i.e., maximum number of Monthly Assessments per participant is 15). Participants can complete their first Daily Assessment (i.e., DA1) on the same day as FA1 (i.e., maximum number of Daily Assessments per participant ~ 540).

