### ERST adaptation and training details

The ERST is a 13-week program developed as an adaptation of the UP [40, 41]. The UP, and therein the ERST, focuses on skill development to offset individual differences that lead to emotional disorders by facilitating an approach-oriented stance toward emotions and reducing reliance on avoidant coping strategies. The ERST frames emotional experiences as natural responses to threat, rather than pathological occurrences to avoid; as such, the ERST is well-suited for mitigating health challenges and the skills may also help PSP to support persons in distress, including other PSP and the community members they all serve.

The RCMP ERST training materials include an instructor guide, didactic PowerPoints, and a trainee workbook. The RCMP ERST [56] was adapted for use by a broader range of PSP based on feedback from our PSP knowledge users (i.e., [name], [name], [name], [name], [name]) and a focus group of PSP stakeholders (i.e., [name], [name], [name], [name], [name]). The focus group was conducted and recorded via Zoom over three sessions. Participants were asked to review the materials prior to the sessions, and then the focus group leader asked a series of questions (e.g., “Bearing this in mind for your particular sector, how realistic do you feel this example is? Is this something that people can relate to?”) to elicit feedback and suggestions from participants. The session transcriptions were used to adapt the materials for use by a broader range of PSP. For example, scenarios related to RCMP cadet training were replaced with yearly continuing education scenarios designed to be relatable for a broad range of PSP. Participants were asked to do a final review of all materials after the initial adaptations were completed. The materials were then revised if needed and sent to the research team ERST leader ([name], a co-developer of the UP) to ensure the adaptations complied with UP fidelity requirements.

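### The stated last T1 and T2 dates are 88 days apart, which conflicts with T2 at about 16 weeks after training starts and barely accommodates the 13-week course

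*Protocol article*

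**What the plan says.** The relevant statements are all in the protocol article.

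- **Data collection time frame** sets the milestones: "pre-training (i.e., T1), post-training (i.e., T2; ~ 16 weeks after training commences"), with T3 one year after T2.
- **ERST adaptation and training details** gives the course length: "The ERST is a 13-week program developed as an adaptation of the UP".
- **Gender and sex**, in scheduling the later focus groups, describes them as held "after T2 (i.e., immediately after program completion").
- **Current study status and impacts of COVID-19** gives the calendar. The first assessments were in autumn 2021, on 20 October. On the baseline visits, the section reports that "T1 data collections for all participants were completed May 23, 2022". Its projection for the post-training visits is this: "The T2 data collections for all participants are expected to conclude by August 19, 2022". It expects the one-year follow-up to be finished by 16 September 2023.

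The second overarching hypothesis (Hypotheses) attributes change from T1 to T2 to the training. The fifth compares T3 with T2. Study design says a randomized trial was not feasible and looks to the separate RCMP Study for results relative to a control group.

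**The concern.** The T1 and T2 sentences both cover all participants, so the last person assessed at T1 is among those whose T2 is due by 19 August 2022. On the stated dates that person has less time between T1 and T2 than the article's own T2 definition requires.

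This matters because there is no concurrent control group. The T1-T2 change can be read as a training effect only if T1 precedes training and T2 follows it. If the training works, a T1 taken after the first session or a T2 taken before the last would shrink the observed change. An early T2 would also move part of the gain into the T2-T3 comparison. Activity schedules were set with each sector's leads (Recruitment and retention), so any mistiming could fall unevenly across sectors and touch the sector-by-time comparison. The article does not show that it does.

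**Working it through.** **Inputs.** Start of data collection, 20 October 2021; last T1, 23 May 2022; last T2 (projected), 19 August 2022; last T3 (projected), 16 September 2023 (all from Current study status). Course length 13 weeks = 91 days (ERST adaptation and training details). T2 at about 16 weeks = 112 days from training start, and T3 at T2 + 1 year (Data collection time frame). The article states no T1-T2 interval in days, so there is no figure to reproduce; the interval follows from the dates.

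**1. Available interval for the last entrant.** 19 August − 23 May 2022 = 88 days = 88/7 = 12.6 weeks. This is a maximum, because that person's T2 can be no later than 19 August.

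**2. Required interval under the 16-week definition.** T1 ≤ training start, and T2 ≈ training start + 112 days, so T2 − T1 ≥ about 112 days. Shortfall: 112 − 88 = 24 days, or 24/112 = 21% of the interval. Any wait between T1 and the first session widens it.

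**3. Who is affected.** The latest T1 that allows a 16-week T2 by 19 August is 19 August − 112 days = 29 April 2022. The definition is approximate; if 14 weeks (98 days) were accepted, which is an assumption, the cut-off would be 13 May, still 10 days before T1 collection ended. T1 collection ran 215 days (20 October 2021 to 23 May 2022), and the conflict concerns the last 24 of them. That is a calendar span, not a share of participants; the article gives no distribution of T1 dates.

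**4. Course completion.** Suppose training began on 23 May, the same day as the last T1.
- Thirteen full weeks: 23 May + 91 days = 22 August, 3 days after the stated last T2.
- Thirteen weekly sessions: the last falls at 23 May + 12 × 7 = 84 days = 15 August, leaving 16 to 19 August for T2.

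A T2 right after completion is thus just possible on the second reading and misses by 3 days on the first.

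**5. Cross-check against T3.** 16 September 2023 − 1 year = 16 September 2022, which is 116 days (16.6 weeks) after 23 May 2022. That matches the 16-week definition. From the stated T2 date, 19 August 2022 to 16 September 2023 is 393 days, 28 more than a year.

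**6. The two descriptions of T2.** T2 at 16 weeks from the start and T2 immediately after a 13-week course differ by 16 − 13 = 3 weeks if the course runs without a break.

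**The case against.** The T2 date is a forecast in a status paragraph, not an assessment rule, and the T3 cross-check suggests that it may simply be wrong. This stands. A reader might infer from the 88 days that some assessments cannot be truly pre- or post-training. The documents do not support that: as step 4 shows, a T1 on 23 May, weekly sessions from that day and a T2 on 16 to 19 August would give a genuine before-and-after pair. What fails then is the 16-week timing, not the pre/post status.

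The T3 date is also an outer limit, so one year from 19 August 2022 plus four weeks to finish would satisfy it. That is fair: T3 fits the 16-week definition better than the T2 date does, but it does not prove the T2 date wrong. The focus-group wording is a passing remark, and the article does not say that the course runs in 13 unbroken calendar weeks, so the 3-week difference between the two descriptions is weak evidence by itself.

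The number affected is unknown. A single T1 on the last day would produce the 88-day gap, and withdrawal of the latest entrants before T2 would narrow or remove it.

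Finally, visit windows and time coding are commonly left to a full protocol or SAP, neither of which is shown. Their absence is not the finding. The finding is that dates and definitions stated in this article do not agree. The suggested analysis is a safeguard for the contrast most exposed to that disagreement.

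**Conclusion.** The inconsistency is real and should be fixed. The stated last T1 and T2 dates fall 24 days short of the 16-week definition for the last entrant and conflict with it for anyone with T1 after about 29 April 2022. For the 13-week course the margin runs from 3 days too few to 4 days spare, depending on how 13 weeks is counted and assuming training started on the day of T1. The arithmetic is exact. It rests on the stated dates being correct and on the last T1 participant remaining in the study to T2.

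The article does not show whether the projected date is wrong, T1 was late or T2 was early, nor how many people are involved. So no bias in the study estimate can be calculated. A reader might reason that a baseline 24 days into a 91-day course already holds 24/91 = 26% of the effect. That would need a correct T2 date, a T2 at exactly 16 weeks, T1 as the mistimed visit and benefit building up evenly, and it would describe only the last entrant.

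**What to change.** 1. Reconcile the T1, T2 and T3 dates in Current study status with the T2 descriptions in Data collection time frame and in Gender and sex, and with the course length. If the T2 date is a slip, a corrected date and a single T2 definition settle the text.
2. Derive the timing of each Full Assessment from its actual date relative to that participant's first and last training session, and report how many FA1s are dated after the first session and how many FA2s before the last.
3. Report a sensitivity analysis of the T1-T2 change, for example with actual time since training start as the time variable, or excluding those FA1s and FA2s.

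The cost is a wording correction, one variable derived from assessment and session dates, and possibly a few lost T1-T2 pairs in the sensitivity analysis. The main analysis need not lose any data.
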